## Abstract

**Background:**

Despite the widespread use of external ventricular drainage, revision rates, and associated complications are reported between 10 and 40%. Current available image-guided techniques using stereotaxy, endoscopy, or ultrasound for catheter placements remain time-consuming techniques. Recently, a smartphone-assisted guide with high precision has been described. The development of an easy-to-use, portable, image-guided system could reduce the need for multiple passes and improve the rate of accurate catheter placement. This study aims to prospectively compare in a randomized controlled manner the accuracy of the freehand pass technique versus an easy-to-use, portable, adjustable guiding device for ventriculostomy catheter placement.

**Methods/Design:**

This is a single center, prospective, randomized trial with a blinded endpoint (ventricular catheter tip location) assessment. Adult patients with the indication for ventriculostomy, as proven by computed tomography (CT), will be randomly assigned to the treatment group or the control group. For patients in the treatment group, ventriculostomy will be performed using an adjustable guiding device and DICOM (Digital Imaging and Communications in Medicine) image-reading software assistance (for example, using a mini-tablet) based on preoperative CT imaging.

Patients in the control group will receive standard freehand ventriculostomy using anatomical landmarks. The catheter may be placed for external drainage or internal (ventriculoperitoneal) shunting in both groups. The primary outcome measure is the rate of correct placements of the ventricular catheter, defined as a score of 1 to 3 on grading system for catheter tip location on a postoperative CT scan. Participants will be followed for the duration of hospital stay, an expected average of two weeks. The primary outcome will be determined by one of the authors blinded to the treatment allocation. We aim to include 236 patients in three years. Secondary outcome measures include: frequency of placements required, frequency of completed placements within the ventricle of the perforated part of the catheter tip, frequency of very early and early shunt failures (revision of the ventricular drainage within 24 hours and within the hospital stay), frequency and percentage of complications (procedure-related and nonsurgical) at discharge.

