### Outcome assessment

#### Primary outcome measures

The first primary outcome measure will be the frequency and percentage of correct placements of the ventricular catheter, assessed by the three-point scale of Kakarla *et al*., with an additional 1a/1b criteria (Table 
1)
[21]. The effect size will be measured using relative risk, absolute risk reduction, and numbers needed to treat. The second primary outcome measure will be the frequency and percentage of acute ventricular revisions (within one week for an improperly placed catheter). Assessment is performed by an investigator blinded to the study allocation. The effect size will be measured using relative risk, absolute risk reduction, and numbers needed to treat.

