**Table 1 Tab1:** **Grading system for catheter tip location**
[21] **with additional grades 1a/1b**

Grade	Accuracy of placement	Location of catheter tip
1	Optimal/adequate	Ipsilateral frontal horn, including tip of third ventricle: 1a, no contact with ventricle wall; 1b, contact with ventricle wall
2	Suboptimal in non-eloquent tissue	Contralateral frontal horn or lateral ventricle/corpus callosum/interhemispheric fissure
3	Suboptimal in eloquent tissue	Brainstem/cerebellum/internal capsule/basal ganglia/thalamus/occipital cortex/basal cisterns

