## Discussion

Studies assessing catheter malplacement find a high percentage of cases of misplacement. Following head trauma, mass lesions, or in slit ventricles, there is a situation of altered anatomy, rendering catheter placement difficult. For example, the ventricles may be compressed and deviated and therefore difficult to cannulate. Furthermore, if the ventricular catheter is placed in the context of a shunt, high revision rates add to patient morbidity and procedural costs. As there is a need to improve current practices in the placement of ventricular catheters, this VENTRI-GUIDE protocol aims to assess if a portable, easy-to-use, mini-tablet-assisted guide for ventriculostomy can increase the accuracy of ventriculostomy in comparison with the freehand pass technique. Our primary outcome is the rate of correct placements of the ventricular catheter, measured using a three-point grading scale for the outcome of each ventriculostomy.

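### The only stated definition of correct placement covers every grade of the scale, so the first primary outcome has no usable cut-off

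*Protocol article*

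**What the plan says.** The Abstract (Methods/Design) makes the rate of correct placements the primary outcome, "defined as a score of 1 to 3 on grading system for catheter tip location on a postoperative CT scan".

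Table 1 lists the whole scale:
- Grade 1, optimal/adequate: "Ipsilateral frontal horn, including tip of third ventricle: 1a, no contact with ventricle wall; 1b, contact with ventricle wall".
- Grade 2: "Suboptimal in non-eloquent tissue". This covers the contralateral frontal horn or lateral ventricle, the corpus callosum and the interhemispheric fissure.
- Grade 3: "Suboptimal in eloquent tissue". The sites are "Brainstem/cerebellum/internal capsule/basal ganglia/thalamus/occipital cortex/basal cisterns".

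The other sections that mention the outcome give no threshold. Primary outcome measures states: "The first primary outcome measure will be the frequency and percentage of correct placements of the ventricular catheter". It adds that this is assessed on a three-point scale "with an additional 1a/1b criteria". Reporting and statistical analysis refers only to the number and frequency of correct ventriculostomies. The Discussion says the outcome is "measured using a three-point grading scale for the outcome of each ventriculostomy".

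Primary outcome measures also names a second primary outcome: acute ventricular revisions within one week for an improperly placed catheter.

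Sample size analysis plans on a ventricle hit rate of 69.2% freehand (31% misses), a relative risk of 0.5 and an absolute reduction of 15.5 points. It asks for 118 patients per arm at 80% power.

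**The concern.** A binary endpoint needs a rule that lets some patients fail. The one rule given takes in the whole scale, so a tip in the brainstem counts as correct. The relative risk of correct placement would then be 1 among graded catheters, the absolute risk reduction 0, and the number needed to treat undefined. All three are the effect measures that the plan promises for this outcome. The rule also conflicts with the sample size, which expects about three in ten freehand placements to miss.

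If the phrase is set aside as a slip, no threshold remains. The choice could then be made after grades are known, including at the efficacy interim, which tests the primary outcomes after 60 patients per arm.

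**Working it through.** **1. Set the rule against the scale.** Grades in Table 1: {1 (1a, 1b), 2, 3}. Grades counted as correct in the Abstract: {1, 2, 3}. The two sets are the same, so P(correct | graded) = 1 in each arm.

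**2. Reproduce the planned sample size.** Inputs from Sample size analysis: p1 = 0.31, p2 = 0.155, 80% power, two-sided 5% (the text calls it a 95% significance level). Pooled-variance formula without continuity correction, with p̄ = (p1 + p2)/2 = 0.2325:

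n = [1.960·√(2p̄(1−p̄)) + 0.8416·√(p1(1−p1) + p2(1−p2))]² / (p1−p2)²

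= [1.960 × 0.5974 + 0.8416 × 0.5873]² / 0.155²

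= (1.1709 + 0.4943)² / 0.024025 = 115.4, so 116 per arm.

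With 30.8% versus 15.4% it gives 117. Both agree with the stated 118 to within two patients, and power at 118 for 31% versus 15.5% is 80.9%. The arithmetic is sound. The fault is in the endpoint it is attached to.

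**3. Apply the Abstract's rule.** Success is 100% versus 100% among graded catheters. The difference and its variance are both 0, and the two-proportion test is undefined. The planned 15.5-point difference cannot occur.

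**4. Allow for ungraded catheters.** A missing CT, or a tip at a site Table 1 does not list, might be counted as a failure, although no rule says so. Assuming 1%, 2% or 5% such failures freehand and a relative risk of 0.5, power at 118 per arm is about 6%, 9% or 17%.

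**5. Try a grade-1 cut-off.** The planning rates are ventricle hits. Grade 2 mixes a hit (contralateral ventricle) with misses (corpus callosum, interhemispheric fissure), so neither grade 1 alone nor grades 1 and 2 together equals a ventricle hit. The 31% therefore does not carry over.

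The documents give no grade-1 rate for this centre. The nearest figures are in the 90-patient retrospective series in the Background: 56% in the ipsilateral lateral ventricle and 8% in the third ventricle. As a rough guide, that leaves 100 − 56 − 8 = 36% or 100 − 56 = 44% outside grade 1, depending on how third-ventricle tips count. Sample size analysis cites malpositioning of 25% to 45% in other studies. With an assumed relative risk of 0.5 and the formula above:

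| Assumed freehand failure | Guided failure | n per arm for 80% | Power at 118 per arm |
|---|---|---|---|
| 25% | 12.5% | 152 | 69% |
| 31% | 15.5% | 116 | 81% |
| 36% | 18% | 95 | 88% |
| 44% | 22% | 71 | 95% |
| 45% | 22.5% | 69 | 96% |

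**The case against.** The strongest reply is that this is a drafting slip in an abstract. The phrase may have been meant to give the range of the scale. Table 1 separates optimal/adequate from suboptimal, the sample size plainly expects misses, and a blinded reader would be unlikely to call a thalamic tip correct. That is plausible as to intent. But the sentence defines correct placement, and if it is read as a range the article has no threshold at all. The allowance for a condensed article does not help, because the definition is stated and is wrong as stated.

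A reader might infer something stronger: that power is zero and the trial cannot answer its question. The documents do not support that, for three reasons.
- The second primary outcome does not use the scale. Nor do secondary outcomes such as the number of placements required and early shunt failures.
- Ungraded or unlisted tips could still count as non-successes, so 100% in both arms holds for graded catheters only.
- The failure follows from the literal rule. Any cut-off that lets graded catheters fail restores a working comparison.

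A reader might also infer that naming grade 1 settles everything, with 69% versus 84.5% success still in force. It does not, because those are ventricle-hit rates.

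**Conclusion.** The point holds for the first primary outcome and must be fixed. The only stated success rule counts every graded catheter as correct, contradicts Table 1's labels, and is incompatible with the 31% miss rate behind the 118 per arm. This follows from the text alone.

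The power figures after repair rest on assumptions: a relative risk of 0.5, a freehand failure rate between 25% and 45%, and a two-sided 5% test without adjustment for the interim look. On those terms 118 per arm could be short of 80% or comfortably above it, depending on a grade-1 failure rate that the article does not give.

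**What to change.** Before any catheter is graded, and in any case before the interim analysis, replace the score of 1 to 3 with one explicit cut-off. Use the same sentence in the Abstract, Primary outcome measures, Reporting and statistical analysis, and the Discussion.

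Table 1's labels point to this wording, for the sponsor to confirm: correct placement is grade 1 (1a or 1b); grade 2, grade 3 and any tip location not listed under grade 1 are misplacements. State as well how a patient without a gradable postoperative CT is counted. The split into 1a and 1b can be reported descriptively.

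Then restate the assumed failure rates and the power at 118 per arm on that definition, using grade-level data from the centre's own earlier series if they can be obtained.

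The wording costs one sentence, repeated in four places. Restating the rates takes a short recalculation. It could change the sample size if the grade-1 failure rate proves to be near the lower end of the range.

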The classical freehand technique uses anatomical landmarks and the catheter is placed in the anterior horn of the lateral ventricle through a burr hole just anterior to the coronal suture in the mid-pupillary line (at the level of Kocher’s point; a point on the surface of the cranium 2.5 cm from the midline and 1 cm anterior to the coronal suture, approximately 11.5 cm above the nasion). The target is the ipsilateral frontal horn just anterior to the foramen of Monro to avoid the choroid plexus. The right nondominant side is preferred. The catheter is directed freehand, using external landmarks in the coronal plane towards the ipsilateral medial canthus and in the sagittal plane through the external auditory meatus. A post-procedural CT scan of the brain is performed within 24 hours as part of standard care for postoperative control, or earlier in case of postoperative CSF drainage problems.

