#### Secondary outcome measures

The secondary outcome measures will be the frequency of placements required, the frequency of completed placements within the ventricle of the perforated part of the catheter tip, the frequency of very early and early shunt failures (revision of the ventricular drainage within 24 hours and within the hospital stay), and the frequency and percentage of complications (procedure-related and nonsurgical) at discharge. The effect size will be measured using relative risk, absolute risk reduction, and numbers needed to treat where possible.

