### Data documentation

The following parameters will be recorded and used to demonstrate successful randomization and the presence of even baseline groups (Table 
1):Age (years);Gender (nominal male/female);Glasgow Coma Score on admission (ordinal, 1 to 15-point scale);Cause of hydrocephalus/slit ventricles Preoperative ventricle size - width (millimeters);Preoperative ventricle size - using the frontal occipital horn ratio (FOHR; millimeters);Preoperative ventricle size - and the width of the lateral ventricle in the coronal plane between the medial wall of the corpus callosum and the septum;Preoperative ventricle size - using the Evans ratio (bifrontal ventricular span, the ratio of maximum width of the frontal horns to the maximum width of the inner table of the cranium; millimeters),Episode of care (nominal, *de novo*/revision) Time from symptom onset to *admissi*on (hours);Time from symptom onset to randomization (hours);Time from symptom onset to EVD (external ventricular drainage placement (hours);Duration of hospital stay (days);Duration of EVD being in place (days);Presence of CSF infection during the first 14 days, as defined by modified clinical diagnostic criteria for device-associated meningitis (treatment required on either positive culture, or elevated cell count, red cell:white cell ratio, increased lactate, and/or decreased glucose (nominal, yes/no) [22].The EVD catheter placed for ventriculoperitoneal shunting (nominal, yes/no).Any associated endoscopic procedure, for example, third ventriculostomy (freetext);Neurosurgical experience of primary operator (years).

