### Adverse events and severe adverse events

The term adverse event (AE) describes any sign, symptom, syndrome, or any disease occurring newly in a trial participant after consent to the trial and being of particular interest for the assessment of the disease or the security of the therapeutic concept. Any AE is documented in the CRF or electronic file of the patient.

For the purposes of this trial the definition of an adverse event will consist of any one of the following:Impairment of the general condition of the patient,Physical injury, including falls,Infection other than wound infection, sepsis or Systemic Inflammatory Response Syndrome (SIRS) Intracranial bleeding in the proximity of the ventricular catheter,Wound infection or dehiscence at the emersion site of the ventricular catheter,Newly occurred neurological deficit,Arterial or venous thrombosis,Any suspicious findings that may have relationship to the study.

For the purposes of this study the definition of a serious adverse event (SAE) will consist of any one of the following:Fatal events or death,Any life-threatening condition,Disabling or incapacitating events,Events that require prolongation of hospitalization,Events that require intervention to prevent permanent impairment.

The relation of the AE or SAE (as a cause or result) to any other AE or SAE will be scored on a two-point scale; 0 - no, 1 - possible (brief description), or 2 - yes (give brief description). The investigator’s estimation of the severity of the problem to the study or study device (to be measured only, if the AE or SAE is or might be related to study) will be measured and scored on a three-point scale; 1 - mild, 2 - severe, or 3 – life-threatening. The investigator’s recommendation to change the protocol, informed consent, or assent form will be given as a binary answer of yes (with a brief description) or no. The outcome of AE or SAE will be assessed until discharge using a four-point scale; 1 - full recovery, 2 - permanent deficit, 3 - not yet fully recovered, or 4 - not known.

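### Follow-up that stops at discharge does not secure the one-week revision outcome, and it gives early failure and complications a different time window for each patient

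*Protocol article*

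**What the plan says.** The abstract (Methods/Design) sets the observation period: "Participants will be followed for the duration of hospital stay, an expected average of two weeks". The section on adverse events agrees with it: "The outcome of AE or SAE will be assessed until discharge".

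The outcomes use several different windows:

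- Second primary outcome (Primary outcome measures): "acute ventricular revisions (within one week for an improperly placed catheter".
- Very early and early shunt failure (Secondary outcome measures): "revision of the ventricular drainage within 24 hours and within the hospital stay".
- Complications (Secondary outcome measures): "complications (procedure-related and nonsurgical) at discharge".
- A recorded parameter in Data documentation, not a named outcome: "Presence of CSF infection during the first 14 days".

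Effects on the primary outcomes are to be expressed as relative risk, absolute risk reduction and number needed to treat. The same measures apply to the secondary outcomes where possible. The article describes no contact or data capture after discharge.

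**The concern.** Two separate things go wrong when observation is tied to discharge.

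First, a patient who leaves before day 7 is not observed, under the stated rule, to the end of the window of a primary outcome. That outcome also feeds the interim analysis, which is based on the primary outcomes and adverse events.

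Second, early failure and complications have no fixed window at all. Each patient is at risk of being counted for as long as he or she stays in hospital. Stay is a post-randomisation variable that depends on clinical course; the article's own list of serious adverse event criteria includes "Events that require prolongation of hospitalization". If stay differs between arms, the counts can differ although the underlying risk does not, or a real difference can be hidden. A number needed to treat over an unstated and unequal period is hard to interpret. Randomisation and blinded reading of the CT do not cure this, because the difference in observation time arises after allocation.

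**Working it through.** **1. What does not depend on follow-up.** The sample size rests on catheter placement: 31% misses against 15.5%, two-sided alpha 0.05, power 80%. With the pooled formula,

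n = [1.96·√(2·0.2325·0.7675) + 0.8416·√(0.31·0.69 + 0.155·0.845)]² / 0.155² = 115.4, so 116 per arm.

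With 30.8% against 15.4% it is 117. The stated 118 is reproduced to within 2 patients and contains no follow-up term. Placement is read on an early scan: "A post-procedural CT scan of the brain is performed within 24 hours as part of standard care for postoperative control". That sentence stands in the paragraph on the freehand technique but describes standard care, so I take it to apply to both arms. Failure within 24 hours has its own short, fixed window.

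**2. Windows against observation.**

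| Outcome | Window | Secured by follow-up to discharge? |
|---|---|---|
| Tip placement | CT within 24 hours | Yes |
| Very early failure | 24 hours | Yes |
| Second primary (revision) | 7 days | Not for patients home before day 7 |
| Early failure | Hospital stay | Captured as defined, but the window varies by patient |
| Complications | To discharge | Captured as defined, but the window varies by patient |

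**3. How many patients leave before day 7?** The article gives a mean stay of about 14 days and no spread, so this rests on assumption. With mean 14:

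- Gamma stay, coefficient of variation (CV) 0.33, 0.5, 0.71, 1.0: 4%, 14%, 26%, 39% leave before day 7. At CV 1.0 this is 1 − exp(−7/14) = 0.393.
- Log-normal stay, CV 0.5, 0.75, 1.0: 11%, 24%, 34%.

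Patients discharged are not events missed. If revision times were uniform over the 7 days and independent of discharge, and nothing were captured afterwards, the missed share would be the average of P(stay < t) over t from 0 to 7. For the gamma cases this is 1%, 4%, 10% and 21%. These figures ignore the CT within 24 hours and so probably overstate the loss.

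**4. What a variable window does to early failure.** Assume one constant revision hazard in both arms, 15% per 14 days: h = −ln(0.85)/14 = 0.0116 per day. For a gamma stay with mean m and shape k, the chance of a revision during the stay is 1 − (1 + h·m/k)^(−k).

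| Mean stay (days) | k = 2 | k = 4 |
|---|---|---|
| 10 | 10.7% | 10.8% |
| 12 | 12.6% | 12.8% |
| 14 | 14.5% | 14.7% |
| 16 | 16.3% | 16.6% |

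If mean stay were 10 days in one arm and 14 in the other, the relative risk would be 10.7/14.5 = 0.74. The absolute difference would be 3.8 points and the number needed to treat 1/0.038, about 26, with identical daily risk. With 12 against 14 days the relative risk would be 12.6/14.5 = 0.87. The hazard and the differences in stay are illustrations; the article predicts neither.

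**The case against.** The strongest reply has five parts.

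- *The one-week outcome is little exposed.* It counts only revisions for an improperly placed catheter. The CT within 24 hours, or earlier if drainage fails, should show most malpositions before discharge, and the expected mean stay is twice the window. This stands, and it is why the loss is probably small. The trial is also single-centre and uses electronic patient files, so a readmission there may be on record. The article does not say that such a readmission counts.
- *Early failure and complications are fully captured.* This stands. A reader might infer that events on these outcomes are missed, but they are defined over the stay, so follow-up to discharge finds them all as defined. Their fault is the unequal window.
- *Infection is not an outcome.* A reader might take the 14-day CSF infection item as a named outcome and note that, under the assumed distributions, 54% to 66% of patients would be home before day 14. The item is a recorded parameter outside the primary and secondary outcomes, so that figure does not measure harm to a planned comparison of named outcomes.
- *The feedback is partly circular.* A stay prolonged by a revision adds nothing to a yes/no revision count, because that patient already counts. This stands. Distortion needs stay to differ between arms among patients not yet revised, and no passage predicts that the guide shortens stay. The exposure is nevertheless open by design.
- *The article is condensed.* Arrangements for capture after discharge may be in a fuller protocol. That softens the one-week point. It does not touch the variable window, which the article's own outcome definitions create.

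**Conclusion.** The point holds in limited form and is worth correcting. Observation to discharge does not guarantee the one-week window of the second primary outcome. Early failure and complications have patient-specific exposure fixed after randomisation, so their relative risks and numbers needed to treat lack a common time horizon.

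The documents do not show that one-week events will be lost. How many could be depends on the spread of stay, which is not given, and on how many malpositions the early CT fails to bring to attention. Nor do they show a bias in favour of either arm: the illustrated relative risk of 0.74 requires an assumed four-day difference in mean stay. It would also be too broad to say that every effect measure lacks a time horizon. Placement, 24-hour failure and one-week revision each have one. The first primary outcome and the 118 per arm stand as they are.

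**What to change.** - State that one-week revision is counted from the procedure to day 7 for every randomised patient, whether or not the patient has been discharged.
- In Secondary outcome measures, keep the 24-hour window. Replace the in-stay window for early failure and the discharge time point for complications with one fixed window from the procedure. Fourteen days is a natural example, since the article already records CSF infection over that period. In-stay events after the window can still be listed descriptively.
- Amend the follow-up sentence in the abstract and the adverse event section to match, and say how deaths within the window are counted.
- For patients already home, complete the window by record review or one call.

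The cost is a change of wording and some site time, modest in a single-centre trial of 236 patients. The sample size and the placement outcome do not change.
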